#### Procedure for unblinding if needed

As this is an open-label study, no standard procedure for unblinding is required during routine operations. However, if a serious adverse event or exceptional circumstance arises that necessitates revealing a participant’s group assignment, the principal investigator may access the randomization record. Any instance of unblinding, along with its rationale, will be documented and reviewed to ensure adherence to study protocols and ethical standards.

### Data collection and management

#### Plans for assessment and collection of outcomes

Baseline structured interviews will be conducted prior to randomization to collect data on demographic characteristics, social capital, physical and mental health status, health service utilization, justice system involvement, functionality, and employment and financial history [21]. Validated instruments with established psychometric properties and Spanish versions will be used at baseline and follow-up assessments. These include the Brief Psychiatric Rating Scale (BPRS) for psychiatric symptoms [22], the Medical Outcomes Study Short-Form 12-Item (SF-12) for physical and mental health [23], the Social and Occupational Functioning Scale (SOFS) for functioning and role performance [24], and the Recovery Assessment Scale (RAS-24) to assess perceived recovery and empowerment [25]. All instruments will be administered by trained research staff using structured protocols to ensure consistency and data quality.

Quarterly structured follow-up interviews will assess employment status during the prior 3 months. Data collected will include job titles, employment dates, hours worked, and wages earned. When applicable, the reason and timing of job termination will also be recorded [21]. These structured interviews will be conducted in person at the Center for Comprehensive Care in Long-Stay Mental Health, subject to public health restrictions. If a participant is unavailable, the research team will make multiple contact attempts within the same data collection window. Missed interviews will be documented, and retrospective data will be gathered at the next opportunity.

Follow-up structured research interviews scheduled at 6- and 12 months after randomization, the follow-up interviews will augment the quarterly employment interviews and include measures of health and functionality mirroring those administered at baseline. Additional data collected describes housing, social capital, and health service utilization [21]. Follow-up interviews will be conducted at the same time as the corresponding quarterly employment interviews. As with the quarterly employment interviews, when participants are unavailable for follow-up interview, the research assistant will make several efforts to track and schedule the interview within the designated time until the next quarterly interview period.

IPS fidelity will be assessed using the 25-item IPS Fidelity Scale (IPS-25), a validated instrument with strong internal consistency and predictive validity [26]. Fidelity assessments will take place at approximately 6 and 12 months after program initiation. Experienced IPS reviewers will conduct in-person evaluations, including interviews with IPS staff, clinical team members, administrators, clients, and family members. Observations will cover vocational unit meetings, team discussions, and employer engagements. Reviewers will also examine selected participant records. Results will be used to monitor fidelity, highlight areas for adaptation, and guide ongoing quality improvement efforts.

The IPS Participation Measure is a brief form completed monthly by IPS Employment Specialists to track client engagement and services delivered (e.g., job search, career profiling, support provision) [21]. This tool captures information on employment status, IPS service participation, and reasons for non-participation [27]. IPS Employment Specialists will complete and submit the form monthly for each participant assigned to them. This measure was used with high completion rates in the Supported Employment Demonstration project and allows for the monitoring of IPS adaptations over time [28]. Tracking participation status and reasons for disengagement will support ongoing efforts to improve participant engagement in the IPS program.

Each month, IPS Employment Specialists will complete a service log documenting IPS activities performed during the previous week. This time-sampled approach has shown greater reliability than continuous measurement methods. Logs will capture time spent on various service categories, including direct versus indirect services, community-based versus in-office activities, collaboration with clinic-based mental health staff, job development (e.g., in-person employer meetings), and the delivery of job support. These data will allow for comparisons with current IPS program standards associated with high fidelity. Additionally, the information will help assess the extent to which IPS service delivery has been adapted through the Dynamic Adaptation Process.

External interviewers with experience in clinical and social assessments will be recruited and trained prior to data collection. Both interviewers and IPS employment specialists will enter data using standardized online forms stored on a secure server. Centralized data entry will enable the study analyst to monitor data quality, identify missing or incorrect entries, and adjust data collection procedures as needed to ensure data integrity. All data collection activities will comply with the confidentiality protocols of the Center for Comprehensive Care in Long-Stay Mental Health.

Each quarter, the IPS Supervisor will receive a summary report based on the IPS employment specialists’ service logs. These summaries will support monitoring of IPS implementation and help identify areas requiring adjustment in collaboration with the IPS central team. The IPS Trainer will also receive the reports to assist the Supervisor in addressing challenges and reinforcing adherence to core IPS principles.

#### Plans to promote participant retention and complete follow-up

This study enrolls clients who are already receiving services at the participating site and have established relationships with clinical providers. Combined with pre-recruitment informational sessions and the ongoing engagement of clinicians and research staff, this approach has yielded high retention rates—exceeding 90% at 1- and 2-year follow-up—in similar studies. However, given the limited precedent for IPS implementation in Mexico, we account for a more conservative retention estimate. For example, the Supported Employment Demonstration reported a 77% 1-year IPS participation rate [28]. Accordingly, we anticipate a retention rate of approximately 77%, and this figure informed our sample size and recruitment planning to ensure adequate follow-up data.

To maximize retention and minimize attrition, we will implement several strategies: clearly explaining study requirements prior to enrollment; conducting assertive outreach; collecting updated locator information at each contact point; maintaining regular communication; and providing compensation for each completed interview. Participants will remain eligible for follow-up assessments regardless of their level of engagement with IPS services. Prior studies suggest that participants often stay engaged due to a desire to share their experiences and contribute to the improvement of mental health services.

## Data management

All trial data will be entered into a REDCap database [29] hosted by the research site. The system will track the completion of all study forms, including baseline, quarterly, and final assessments, as well as IPS participation data. Access will be password-protected, and users will only be able to access their assigned records. Any data entry errors will be corrected by authorized research staff, who will document the changes and the reasons for each correction. REDCap automatically maintains an audit trail of all edits and user activity. The Principal Investigator (PI) or designee will implement a data verification protocol and generate reports at the end of enrollment to monitor recruitment progress and assess covariate balance across study arms. The study statistician will review data completeness and IPS participation quarterly. At the end of the trial, data will be exported from REDCap as self-documenting SAS files for cleaning and analysis.

### Statistical methods for primary and secondary outcomes

Primary feasibility outcomes will be analyzed descriptively. Recruitment and retention will be summarized as proportions with 95% confidence intervals. Fidelity scores will be summarized using total and domain scores at each assessment point. Acceptability findings will be integrated descriptively with qualitative data. Quantitative analyses will follow an intent-to-treat approach. Employment, financial well-being, and health-related outcomes will be analyzed using linear generalized mixed models, accounting for clustering at the site level. Effect sizes will be reported with 95% confidence intervals to assess the direction and magnitude of potential impacts. Preliminary analyses will examine data distributions and apply transformations where necessary. Baseline characteristics will be summarized descriptively by randomized group to describe the study sample. No statistical tests will be conducted to compare baseline variables between groups, as any differences are expected to occur by chance due to randomization. Where appropriate, pre-specified prognostic covariates may be included in adjusted models to improve precision of effect estimates. Secondary analyses will include employment trajectories, non-vocational outcomes, and analyses based on level of exposure to the intervention. Longitudinal data will be analyzed using mixed-effects models. Time-to-event outcomes will be evaluated using Kaplan–Meier curves and Cox proportional hazards models.Qualitative data will be analyzed using a flexible coding approach. An initial multilevel codebook (systemic, organizational, provider, participant) will guide the deductive phase of coding, followed by the identification of inductive codes emerging from transcript review. Coding will be conducted by multiple team members who will meet regularly to refine the codebook and resolve discrepancies through discussion and consensus. Once coding is complete, excerpts will be organized into a structured matrix to compare perspectives across stakeholder groups and to identify salient barriers, facilitators, and implementation needs. This analytic strategy is consistent with methods used in the Preparation Phase and follows established approaches in implementation science.

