#### Primary feasibility outcomes

Recruitment and retention rates: the study will monitor the number of participants enrolled and retained throughout the trial to assess whether the target sample size can be achieved within the planned timeframe.Fidelity of IPS implementation: adherence to core IPS principles will be measured using the IPS Fidelity Scale.Acceptability and perceived barriers: qualitative interviews and focus groups with stakeholders (e.g., participants, providers, employers) will explore the acceptability of the IPS model and perceived barriers to its implementation.

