#### Progression criteria for a future definitive trial

Progression to a future definitive trial will be guided by a pre-specified traffic-light framework across four feasibility domains: recruitment, retention, IPS fidelity, and acceptability. Transparent “red–amber–green” thresholds will guide decisions regarding continuation, amendment, or discontinuation of a future trial (Table 4).Recruitment will be assessed as the proportion of achieved versus planned recruitment at matched timepoints during the recruitment period. Recruitment performance will be classified as green if ≥ 85% of the planned recruitment target is achieved, amber if 70–84% is achieved, and red if < 70% is achieved.Retention will be evaluated at the primary follow-up timepoint (12 months). Retention will be classified as green if ≥ 77% of participants are retained, consistent with the retention benchmark anticipated in the study protocol, amber if retention is 60–76%, and red if retention is < 60%.IPS fidelity will be assessed using the IPS-25 Fidelity Scale, a validated instrument widely used to evaluate adherence to the IPS model. Fidelity will be classified as green if the program achieves a score ≥ 100 (indicating good fidelity), amber if scores fall between 74 and 99 (fair fidelity requiring improvement), and red if scores are ≤ 73 (not IPS fidelity).Acceptability will be evaluated using a combination of quantitative participant ratings and qualitative interview data. Quantitative acceptability ratings will be summarized descriptively, and qualitative findings will be interpreted within established implementation science frameworks. Acceptability will be classified as green when quantitative ratings indicate generally favorable perceptions and qualitative data reveal no major barriers to participation; amber when mixed perceptions or remediable barriers are identified; and red when qualitative evidence identifies substantial concerns or barriers that would likely preclude successful implementation of a definitive trial.

**Table 4 Tab4:** Pre-specified progression criteria for feasibility outcomes

Feasibility domain	Green (proceed)	Amber (amend)	Red (stop/reconsider)
Recruitment	≥ 85% of target recruitment achieved	70–84% achieved	< 70% achieved
Retention (12 months)	≥ 77% retained	60–76% retained	< 60% retained
IPS fidelity (IPS-25 scale)	≥ 100 (good fidelity)	74–99 (fair fidelity)	≤ 73 (not IPS fidelity)

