#### Recruitment

The study will implement several recruitment strategies over a 12-month period to enroll 120 participants with 1 year of planned follow-up. Clinicians at the Center for Comprehensive Care in Long-Stay Mental Health will identify potential participants during routine care and refer them to informational sessions offered by the psychosocial rehabilitation service. Promotional materials (e.g., posters and flyers) will be placed in waiting areas and hallways to raise awareness.

Research staff will conduct informational sessions and provide individual outreach to support ongoing recruitment. Individuals who attend a session and express interest in employment will be screened for eligibility, complete the informed consent process, undergo randomization to either usual care or the adapted IPS intervention, and complete the baseline assessment.

Recruitment projections are based on previous IPS trials that achieved consistent enrollment through sustained collaboration with clinical teams and use of incremental recruitment targets [20]. Participant feedback and service utilization data will be used to refine recruitment procedures throughout the study.

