### Assignment of interventions: allocation

#### Sequence generation

This study follows a randomized, controlled, outcome-assessor-blinded, parallel-group design. To ensure balance between the intervention (IPS) and control (Usual Care) groups, permuted block randomization with a block size of four will be used. Accounting for an expected 25% attrition rate, the study will recruit 160 participants, arranged in 40 blocks, to meet the target sample size of 120 participants.

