An additional limitation is that the specific thresholds used within the traffic-light progression framework were not empirically calibrated for this setting prior to the pilot trial. Although the criteria were defined a priori and informed by methodological guidance for external pilot studies, feasibility benchmarks often require refinement once empirical data from the pilot become available. In line with current recommendations, progression criteria in pilot trials should be interpreted as decision-support guidelines rather than rigid statistical rules and may be refined using the evidence generated during the pilot phase. Therefore, the thresholds proposed in this study will be interpreted alongside qualitative findings, implementation context, and fidelity assessments when determining readiness for a future definitive trial [35].

Maintaining fidelity to the IPS model is another key challenge in low- and middle-income settings, where staffing patterns, service availability, and labor markets differ from those in high-income countries. The study addresses this by incorporating intensive initial training, ongoing supervision from experienced IPS trainers, structured fidelity assessments, and regular feedback loops between local teams and the IPS Center. These strategies aim to minimize protocol drift while allowing contextually appropriate adaptations.

Although sustainment and scale-up are central topics in the broader IPS and implementation science literature, they are not formal outcomes of this pilot study. Our focus is on early-stage implementation processes and feasibility parameters that will inform later decisions regarding broader system integration. Similarly, adoption is not measured as a primary outcome; instead, we document contextual factors and early indicators that may influence subsequent uptake of IPS within the Jalisco mental health system [36].

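### Recruitment is defined as a count over a fixed target but summarised as a proportion with a 95% confidence interval, which on the natural binomial reading overstates its precision

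*Protocol article*

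**What the plan says.** Three sections of the protocol article bear on this point.

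- **Definition.** Under the progression criteria: "Recruitment will be assessed as the proportion of achieved versus planned recruitment at matched timepoints during the recruitment period". The rating is green at 85% or more "of the planned recruitment target is achieved, amber if 70–84% is achieved", and red below 70%. The list of primary feasibility outcomes also treats recruitment as a number: "the study will monitor the number of participants enrolled and retained throughout the trial", in order to judge whether the target can be reached in the time planned.
- **Summary.** The statistical methods section gives recruitment and retention one shared method: "Recruitment and retention will be summarized as proportions with 95% confidence intervals". It names no interval formula and no separate treatment for recruitment.
- **Planned number.** The Recruitment section says: "The study will implement several recruitment strategies over a 12-month period to enroll 120 participants with 1 year of planned follow-up". The Sequence generation section says: "Accounting for an expected 25% attrition rate, the study will recruit 160 participants, arranged in 40 blocks".

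No section defines a second recruitment measure, such as enrolled among eligible or among those approached.

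**The concern.** A confidence interval for a proportion treats the denominator as a set of independent units, each of which has the event or does not. Retention fits: the units are randomised participants. Recruitment as defined does not. The 120 (or 160) in the denominator is a number the investigators chose, not a group of people who each might or might not enrol. At the matched timepoints the ratio can also exceed 100%. The random quantity is how many people enrol in a given time, so its uncertainty is that of a count or a rate.

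The stake is how well the pilot appears to know its recruitment performance. Recruitment is a primary feasibility outcome and one of four progression domains. The Sample size section gives stable estimates of recruitment as one reason for the number chosen. A binomial interval makes that estimate look firmer than it is, and increasingly so as recruitment nears the target.

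**Working it through.** **Inputs.** From the protocol: target T = 120 over 12 months (Recruitment section) or T = 160 (Sequence generation); thresholds of 70% and 85% (progression criteria); 95% level (statistical methods). Assumed: Poisson accrual, not stopped at target. The protocol gives no accrual distribution.

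**The plan's own figure.** The protocol states no interval for recruitment, so the only figure to reproduce is the recruitment number: 120 / (1 − 0.25) = 160, and 160 / 4 = 40 blocks. Both match. (The retention section says "we anticipate a retention rate of approximately 77" per cent; with that rate the figure would be 120 / 0.77 = 155.8, so 156.)

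**Formulas.** For x enrolled and p = x/T:

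- Binomial 95% interval for x/T: exact (Clopper-Pearson) and Wilson, since no formula is named.
- Exact Poisson limits for the count: χ²(0.025; 2x)/2 and χ²(0.975; 2x + 2)/2, each divided by T.
- Approximate check: the binomial standard error is √(p(1 − p)/T) and the Poisson standard error of x/T is √(p/T), so the ratio is 1/√(1 − p). This does not depend on T: 1.83 at 70%, 2.58 at 85%, 4.47 at 95%.

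**Results.**

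| T | x | x/T | Exact binomial | Wilson | Exact Poisson / T | Width ratio (vs exact, vs Wilson) |
|---|---|---|---|---|---|---|
| 120 | 84 | 70% | 61.0–78.0% | 61.3–77.5% | 55.8–86.7% | 1.81, 1.90 |
| 120 | 102 | 85% | 77.3–90.9% | 77.5–90.3% | 69.3–103.2% | 2.50, 2.65 |
| 120 | 114 | 95% | 89.4–98.1% | 89.5–97.7% | 78.4–114.1% | 4.11, 4.38 |
| 160 | 112 | 70% | 62.3–77.0% | 62.5–76.6% | 57.6–84.2% | 1.81, 1.89 |
| 160 | 136 | 85% | 78.5–90.1% | 78.7–89.7% | 71.3–100.5% | 2.51, 2.64 |
| 160 | 152 | 95% | 90.4–97.8% | 90.4–97.4% | 80.5–111.4% | 4.15, 4.41 |

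**Coverage.** With T = 120 and a Poisson count, the nominal 95% exact binomial interval covers the true ratio in 74.8% of trials when that ratio is 70%, 57.2% at 85% and 36.1% at 95%. Counts above 120, where no binomial interval exists, are scored as misses; they occur in 0.0%, 3.6% and 26.8% of trials. Leaving them out gives 57.2/96.4 = 59% at 85% and 36.1/73.2 = 49% at 95%, still far below nominal. The Poisson interval covers about 95% in all three cases.

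**As a rate.** 102 enrolled in 12 months is 8.5 per month. The Poisson limits are 0.693 × 120 / 12 = 6.9 and 1.032 × 120 / 12 = 10.3 per month, against a planned 120 / 12 = 10.

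**Denominator.** The same 102 is 102/120 = 85% (green) but 102/160 = 64% (red).

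**The case against.** The strongest reply is that the protocol never says binomial. It names no formula, and the formula is commonly left to a statistical analysis plan, which is not shown. The methods section also does not say that its recruitment proportion is the progression ratio. The flow from referral through screening to consent would supply real denominators, and for enrolled among eligible the sentence would be right. Part of this stands: the overstatement is conditional on the natural reading. But the protocol defines only one recruitment measure, describes it as a proportion, and pairs it with retention under one method. The complaint is that the stated summary does not fit the stated measure, not that detail is missing.

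Four stronger readings are tempting, and the document does not support them.

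- **That a rating would change.** At 102 of 120 the count-based interval runs from just inside red to above target. The rule, however, is applied to the achieved percentage, and the Discussion says that "progression criteria in pilot trials should be interpreted as decision-support guidelines rather than rigid statistical rules".
- **That this interval will set the accrual rate of the definitive trial.** The protocol speaks of generating estimates for planning; it does not say the interval will be used that way.
- **That the understatement is about twelvefold at full recruitment.** At exactly 120 of 120 the exact binomial interval is 97.0–100% and the Poisson one 82.9–119.6%. That comparison fails if enrolment closes at the target, because the count is then fixed and time is what varies. The plan to enrol a set number from a finite sequence makes such closure plausible.
- **That the interval shrinks to nothing at target.** The exact and Wilson intervals are still about 3 points wide there.

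**Conclusion.** The point holds in limited form. The measure is a count over a fixed target, and the planned summary belongs to a different kind of quantity. On the natural binomial reading the reported interval is too narrow, by a factor of about 1.8–1.9 at 70% of target, 2.5–2.7 at 85% and 4.1–4.4 at 95%. These factors hold for either binomial formula and for either target. They rest on Poisson accrual not stopped at target; overdispersed arrivals would make the appropriate interval wider still.

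The consequence is confined to the stated precision of one primary feasibility outcome. The point estimate and the traffic-light colour are unaffected by the choice of interval. The unsettled planned number is different: it can change the colour, so it should be resolved in the same edit.

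**What to change.** In the statistical methods section, separate recruitment from retention:

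- Report participants randomised per month with an exact Poisson 95% interval, allowing for overdispersion if the monthly counts show it. If a percentage of target is wanted, divide the limits for the count by the planned number.
- If enrolment closes on reaching the target, base the rate interval on the time taken. For n participants reached at time t, the limits are χ²(0.025; 2n)/(2t) and χ²(0.975; 2n)/(2t).
- Keep binomial intervals for true proportions, such as retained among randomised and, if reported, consented among eligible.
- State whether the planned number is 120, as in the Recruitment section, or 160, as in Sequence generation.

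The cost is a sentence or two of text and a wider reported interval. No extra data are needed beyond enrolment dates, and the Trial status section says recruitment has not begun.
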